### Adverse events

At the end of each video class, in a pop-up window, all participants will report the intensity of their pain and if there were any adverse events during the session. Participants will be able to contact a therapist through the platform’s email at any time. In case of a severe adverse event related to exercise therapy or MBI (e.g. strains, sprains, persistent severe pain, psychosis, mania, traumatic memories), the participant will be referred to a qualified healthcare professional for further investigation.

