### Interventions

After the baseline assessment, participants will receive immediate access to a WEB platform developed by one of the authors available at http://www.stepslab.com.br/ where the interventions will be delivered. An individualized online meeting will be performed between participants and a physiotherapist not involved in data analysis to guide them regarding platform usage, deadlines and the importance of committing to the intervention. Participants will have access to the online interventions for 8 weeks, which will be immediately ceased at the end of the period. The exercise and education contents will be developed and pre-recorded by two physiotherapists with more than three years of clinical experience using evidence-based material. The MBI content will be developed and pre-recorded by a certified mindfulness teacher with more than 15 years of experience and revised by a psychologist to ensure psychological appropriateness. Details of the interventions according to the TIDier checklist [57] are available in Additional file 2.

Participants will only have access to content related to the group to which they were allocated (restricted area). Each session will be released for access on pre-defined dates relative to participants’ entry into the trial (immediately after baseline assessment). This will be performed by an investigator who will not be involved in the recruitment and assessment of the participants. The system will only allow opening of the next session if the participant had ended the previous one. At the end of each session, participants will be required to report their current level of pain on an online VAS scale, if there was any adverse event during or after the intervention, the level of satisfaction and the level of perceived exertion on a 15-point Borg scale [58], ranging from 6 (no exertion at all) to 20 perceiving a (maximal exertion).

Participants will be instructed to not seek any other kind of knee pain treatment during the study, except in emergency cases. If necessary, participants will be able to contact the therapist through the platform’s e-mail. An outline of the study procedures is summarized in Fig. 1.

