#### Control group

Participants allocated to this group will receive two pre-recorded video classes per week according to their availability (e.g. on Tuesdays and Thursdays) with Exercise therapy and Patient education contents (lasting 35–50 min in total).

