#### Mindfulness group

Participants allocated to this group will receive the same intervention as the control group and an additional pre-recorded video class with MBI content according to their availability (e.g. on Mondays and Wednesdays they receive exercise therapy and Patient education contents; on Fridays they receive mindfulness contents, lasting 35–50 min).

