##### Mindfulness-based intervention

The MBI component will be adapted from Mindfulness-Based Health Promotion (MBHP) model to suit patients with PFP and the online assessments of the present study. MBHP is an 8-week MBI developed in 2009 in the context of health promotion and quality of life [60]. Inspired by Jon Kabat-Zinn’s original protocol—mindfulness-based stress reduction, MBSR (University of Massachusetts Medical Center, USA) [61, 62] —it also aggregates elements of other protocols, such as the MBCT (University of Toronto/Canada; University of Cambridge and Oxford University/United Kingdom) [63], the mindfulness programs of the Breathworks Institute (United Kingdom) [64], and mindfulness-based relapse prevention (MBRP, University of Washington, USA [65]. The MBHP has been extensively used in a variety of health conditions [66–68]. Video classes will include formal and informal mindfulness practices. The description of the MBI is available in Additional file 4. The following themes will be covered.

Week 1: Breaking the automatism.Week 2: Body awareness.Week 3: Leaving the mind and inhabiting the body.Week 4: Raising awareness.Week 5: Letting go.Week 6: Dealing with challenges and letting go of resistance.Week 7: Mindfulness and self-care.Week 8: A look to the future.

In addition, participants included in this group will receive daily reminders and additional material (audios) to continue to practice formal and informal MBHP daily. The participants in this group will be encouraged to practice diaries.

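### The only adverse-event prompt described depends on finishing a class, is scheduled 16 times in Control and 24 times in Mindfulness, and carries two different recall windows

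*Protocol article*

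**What the plan says.** The Adverse events section of the protocol article describes one active way of collecting harms: "At the end of each video class, in a pop-up window, all participants will report the intensity of their pain" and, in the same pop-up, "if there were any adverse events during the session". The Interventions section describes the same end-of-session report but words the question as "if there was any adverse event during or after the intervention". It adds a lock on progress: "The system will only allow opening of the next session if the participant had ended the previous one". Access to the platform stops after 8 weeks.

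Outside the pop-up there is a voluntary route, open to both arms: "Participants will be able to contact a therapist through the platform’s email at any time".

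The arms have different numbers of classes. For Control, "Participants allocated to this group will receive two pre-recorded video classes per week". Mindfulness gets the same two and "an additional pre-recorded video class with MBI content". The Mindfulness arm also receives "additional material (audios) to continue to practice formal and informal MBHP daily", which is practice outside any class.

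Adverse events are not listed under Outcome measures, and the Statistical analysis section describes no between-arm comparison of harms.

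**The concern.** A question asked only at the end of a class is put only to people who reach the end of a class. Someone who stops midway because of a pain flare or distress, and does not come back, does not see the pop-up for that class. Because of the lock, that person sees no later one either. Someone whose problem starts after the last class completed is in the same position. These are the participants a safety record most needs to hear from.

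The number of times the question is asked also depends on the arm. If the report shows a plain count of events, or of participants with at least one event, Mindfulness has had more occasions to report. A reader cannot tell how much of any excess comes from the added sessions and how much from being asked more often.

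The two recall windows make this worse, because they decide what an extra prompt can pick up and whether home practice is covered at all. The trial tests an add-on for which the Adverse events section itself lists psychological harms such as psychosis, mania and traumatic memories. A comparable record of harms in the two arms is therefore worth having even though harms are not an outcome.

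**Working it through.** The protocol states no number of adverse-event prompts, so there is no figure of its own to reproduce. The check uses its schedule.

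**Scheduled prompts per participant** (classes per week × 8 weeks, one pop-up per class)
- Control: 2 × 8 = 16 (Control group section).
- Mindfulness: (2 + 1) × 8 = 24 (Mindfulness group section).
- Ratio: 24 / 16 = 1.50.
- With 31 per arm and full adherence: 31 × 16 = 496 prompts against 31 × 24 = 744.

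This takes exercise and education together as one class, which is the plain reading. If the education video had its own pop-up, one a week would give 24 against 32 (ratio 1.33) and two a week 32 against 40 (ratio 1.25). The imbalance shrinks but remains.

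**Who is not prompted**
- Finishes a class, then stops: prompted for that class and for every earlier completed one.
- Breaks off a class and later returns to finish it: prompted on finishing.
- Breaks off a class and does not return: no prompt for that class and, because of the lock, none afterwards.
- Harm emerges after the last completed class: no further prompt described.

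The last two groups have only the e-mail route.

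**What each recall window covers**
- Adverse events section ("if there were any adverse events during the session"): each prompt covers its own class. The 8 extra Mindfulness prompts then belong to 8 extra sessions, so they mainly track exposure to the add-on. Events between classes are not asked about in either arm, and this includes the home practice that only Mindfulness is given.
- Interventions section ("if there was any adverse event during or after the intervention"): read as including the time since the last class, a delayed event from the shared exercise programme can be reported at three prompts a week in Mindfulness and two in Control. Here the extra prompts can raise reporting without extra exposure.

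**Illustration of size.** The chance p of a reported event per completed prompt is not in the documents, so it is an assumption shown over a range. If p is equal in both arms and prompts are independent, P(at least one report) = 1 − (1 − p)^k, with k = 16 or 24:

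| p | Control | Mindfulness | Ratio |
|---|---|---|---|
| 0.5% | 7.7% | 11.3% | 1.47 |
| 1% | 14.9% | 21.4% | 1.44 |
| 2% | 27.6% | 38.4% | 1.39 |
| 5% | 56.0% | 70.8% | 1.26 |

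The table shows how far the raw proportions separate when the chance per prompt is the same. It does not say how much of the gap is an artefact. Under the session-only window much of it would be real exposure. Under the wider window, reports of one event at successive prompts need not be independent, so the gap could be smaller.

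**The case against.** The strongest reply has five parts.

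1. A reader might infer that participants who stop because of harm are never asked. The text does not support that: anyone who finishes a class is asked at its end, and the therapist e-mail is open throughout. This stands. The gap is limited to harm that interrupts a class without return and harm after the last completed class. For those cases a voluntary e-mail lessens the gap but does not close it.

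2. The extra prompts come with extra sessions, and those sessions are the treatment being added. A higher proportion with events in Mindfulness could be a genuine effect of the add-on, so the tabulated percentages cannot be read as what would be seen with no real difference. This also stands. It is a reason to report sessions completed alongside the counts and to compare on equal intervals. It does not make raw counts comparable.

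3. No between-arm test of harms is planned, and the section describes monitoring and referral. This is correct, and it limits the stakes. Any trial report will still show harms by arm, and those figures will be read as a comparison.

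4. Flares and distress are partly measured by calendar in both arms, through the global rating of change, the pain VAS and the HADS at both follow-ups. The Adherence section also logs unfinished sessions and drop-outs. This helps to identify who stopped, but none of these measures asks about an adverse event.

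5. The article is condensed, and its additional files are not shown. A reader might infer that nothing is asked about harms at 8 weeks or 12 months. The article does not establish that, so the point does not rest on it.

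**Conclusion.** The point holds in a limited form. As described, active collection of adverse events depends on completing classes. It is scheduled 16 times in Control and 24 times in Mindfulness, and it has two recall windows that cannot both apply to the same question. Raw counts are therefore not comparable between arms as collected.

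The ratio of 1.5 assumes full adherence and one pop-up per class. It falls to between 1.25 and 1.33 if education videos are prompted separately, and the ratio actually realised will follow sessions completed. How the excess divides between true exposure and more frequent asking cannot be determined from the protocol.

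A reader might go further and conclude that no safety statement about the mindfulness component is possible. The documents do not support that: completed classes are covered, the e-mail route exists, and counts can be set against sessions completed. The primary outcomes are not affected. The change is worth making because it is cheap and improves both the detection of harm and its comparability. The conflict between the two sections needs resolving whatever a fuller protocol contains.

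**What to change.** - Reconcile the Interventions and Adverse events sections so that both state the same recall window.
- Ask one identical adverse-event question, covering the time since the last report, on a fixed calendar schedule in both arms. Send it regardless of sessions completed.
- Send it separately from the reminders in the Adherence section. Those go out before each session, so they also run at two a week against three, and they may not reach someone who has stopped.
- Put the same question on the 8-week and 12-month online forms, if it is not already there.
- Base any between-arm summary of harms on these equal-interval reports. Keep the pop-up for real-time safety, and report its results with sessions completed as the denominator.

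The cost is one short item on forms that already exist, a separate calendar-based message, a small participant burden and more reports to review.

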### Sample size and power

The sample size calculation was performed based on the usual pain intensity data from Bagheri et al. [30]. Considering a difference between groups of 4.2 mm and a standard deviation of 5.4 mm, with an α of 0.05 and β of 0.20, 26 participants per groups are required (52 in total). We will recruit 31 participants per trial arm to allow for up to a 20% drop-out rate at 12 months.

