**Methods:**

This assessor-blinded, parallel, two-arm randomized clinical trial aims to investigate the effects of adding an 8-week online MBI program to exercise therapy and patient education on clinical and psychological factors for people with PFP. We also aim to investigate whether psychological factors mediate changes in pain and function. Sixty-two participants with PFP will be recruited and randomized into one of two treatment groups (Mindfulness or Control group). Both groups will receive an 8-week intervention involving exercise therapy and education delivered through an online platform. The Mindfulness group will additionally receive a MBI component including formal and informal practices. Outcomes will be assessed online at baseline, intervention endpoint (follow-up 1) and 12 months after intervention completion (follow-up 2). Comparisons between groups will be performed at all time points with linear mixed models. A mediation analysis will be performed using a 3-variable framework.

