### Statistical analysis

Statistical analysis will be performed by the blinded assessor using SPSS software (IBM version 23, SPSS Inc., Chicago, Il). Descriptive statistics will be computed for all variables (e.g. mean, standard deviation). Data will be tested for normal distribution by the Shapiro-Wilk test. Chi-square tests will be performed to compare self-reported recovery (successful x unsuccessful) between groups. For continuous data, the effects of group, time and their interaction will be assessed with linear mixed models. Intraclass Correlation Coefficients will be used to determine the amount of variance explained by random effects [69]. The Bonferroni-adjusted *post hoc* test will be performed for multiple pairwise comparisons where appropriate. Effect sizes (95% CI) (Cohen’s d) will also be calculated and interpreted as follows: Cohen’s = 0.2 ‘small effect’; = 0.5 ‘moderate effect’; = 0.8 ‘large effect’ and = 1.3 ‘very large effect’ [70]. Intent-to-treat analyses will be performed for all outcomes. Multiple imputation will be used to account for missing data if the proportion of missing data is > 5% [71]. For all tests, an α level of 0.05 two-tailed will be adopted to indicate statistical significance.

The mediation effects will be assessed following the 3-variable framework described by MacKinnon et al. [72]. In this model, the intervention condition is assumed to have both direct and indirect paths to the changes in clinical outcomes. The indirect path passes through the potential mediators (anxiety, depression, kinesiophobia, pain catastrophizing and pain self-efficacy). Three multiple regressions will be performed: [1] to test the association between the predictor (i.e., interventions) and the outcomes (i.e., pain and function); [2] to test the association between the predictor and the potential mediators and [3] to test the association between the potential mediators and the outcomes after controlling for the predictor. Then, it will be observed whether the association of the predictor with the outcome after controlling for potential mediators will be smaller than observed in the first regression.

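### Recruiting 31 per arm does not cover the stated 20% drop-out: 24.8 per arm would remain against the 26 required, and the most it can absorb is about 16%

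*Protocol article*

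**What the plan says.** The Sample size and power section bases the calculation on usual pain intensity: "Considering a difference between groups of 4.2 mm and a standard deviation of 5.4 mm", "with an α of 0.05 and β of 0.20". From this it concludes that "26 participants per groups are required (52 in total"). The next sentence adds the allowance for loss: "We will recruit 31 participants per trial arm to allow for up to a 20% drop-out rate at 12 months". The Methods part of the Abstract gives the same total: "Sixty-two participants with PFP will be recruited and randomized into one of two treatment groups". The Statistical analysis section fixes the test as two-sided ("an α level of 0.05 two-tailed will be adopted to indicate statistical significance"), and Randomization and blinding gives 1:1 allocation. The article states no other required number and no other inflation rule.

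**The concern.** The article gives a number required (26), a number recruited (31) and a drop-out rate that the difference is meant to cover (20%). A drop-out rate is a fraction of those enrolled, so the required number has to be divided by the proportion retained, 0.80. Thirty-one is instead close to 26 multiplied by 1.20.

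What is at stake is a stated property of the design. The long-term effect at 12 months is one of the trial's aims, and the allowance is set for that time point. Anyone who later compares actual retention with this sentence would take a loss of 17% to 20% as leaving the required number, when it does not. The base figure also has almost no slack, so a shortfall in the retained number takes power below the planned level at once.

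**Working it through.** **Inputs**

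- Difference 4.2 mm, standard deviation 5.4 mm, α 0.05, β 0.20 (Sample size and power)
- Two-sided test (Statistical analysis)
- 1:1 allocation (Randomization and blinding)
- Required 26 per group, recruited 31 per arm, drop-out up to 20% at 12 months (Sample size and power); 62 in total (Abstract)

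**Step 1: the plan's base figure**

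Normal approximation for two means:

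n per arm = 2 × (1.96 + 0.8416)² × (5.4/4.2)² = 25.95, rounded up to 26.

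This reproduces the stated 26. A two-sample t test gives 26.94, so 27. A one-sided test gives about 21 and does not fit. The article does not name its formula; the normal approximation is the one that returns exactly 26.

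**Step 2: what 31 per arm leaves after 20% loss**

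- Per arm: 31 × 0.80 = 24.8, below 26.
- In total: 62 × 0.80 = 49.6, below 52.
- In whole people: the largest loss within 20% is 6 of 31 (19.4%; 7 of 31 is 22.6%). That leaves 25 per arm, still one short.

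**Step 3: the drop-out that 31 per arm does cover**

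1 − 26/31 = 5/31 = 16.1%.

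**Step 4: the number that 20% would need**

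- Per arm: 26/0.80 = 32.5, so 33 per arm, 66 in total.
- Check: 33 × 0.80 = 26.4, which is at least 26.
- Inflating only the total: 52/0.80 = 65.

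The planned 62 is therefore 3 or 4 short, depending on where the rounding is done. The stated 31 matches 26 × 1.20 = 31.2 rounded down. That is a likely explanation, but the article does not show this step.

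**Step 5: the effect on power**

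The standardized difference is 4.2/5.4 = 0.778. On the normal approximation, power = Φ(0.778 × √(n/2) − 1.96).

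| Retained per arm | Normal approximation | t test |
|---|---|---|
| 26 (stated as required) | 80.1% | 78.5% |
| 25 (6 of 31 lost) | 78.5% | 76.9% |
| 24.8 (20% of 31 lost) | 78.2% | 76.5% |

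Compared within one method, going from 26 to 24.8 costs 80.1 − 78.2 = 1.9 points (normal) or 78.5 − 76.5 = 2.0 points (t test). The remaining gap between 76.5% and 80% comes from the choice of formula and not from drop-out.

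**The case against.** The strongest case on the other side is that the shortfall is slight and may be partly recovered by the analysis. Counted in whole people it is one participant per arm, and power falls by about 2 points. No conclusion of the trial has been shown to depend on it. The power figures also treat participants who drop out as contributing nothing, whereas the Statistical analysis section plans intention-to-treat analyses with linear mixed models, and multiple imputation if more than 5% of data are missing.

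The possible recovery can be sketched. Assume that data are missing at random and that the correlation ρ between earlier and 12-month pain is known. The variance of a 12-month arm mean is then multiplied by about 1 − 0.2ρ². The 24.8 completers match 26 when 1 − 0.2ρ² = 24.8/26 = 0.954, that is at ρ of about 0.48. The article gives no value for ρ and does not use this argument to justify 31. It may reduce the loss of power, but it does not make the sentence correct, because the sentence compares head counts.

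Two further points can be made. First, the article does not tie its power calculation to one time point. That is true, but it does place the 20% at 12 months, and it is there that the count fails. Second, 20% might be read as an addition on top of 26. That is not what a drop-out rate among recruited participants means, and on that reading too 31.2 should have been rounded up to 32, not down to 31.

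What stands is that the effect is small and that the loss of power is an upper bound under the sketched model. The arithmetic itself is not in dispute.

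**Conclusion.** The point holds. On the article's own figures, 31 per arm does not allow for 20% drop-out. It retains the required 26 only up to 16.1%, and at 20% it leaves 24.8 per arm (25 in whole people). A 20% allowance corresponds to 33 per arm, 66 in total.

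The head-count result needs no assumption beyond the three printed numbers. The power result (78.2% on the normal approximation, 76.5% on a t test) also assumes the stated difference and standard deviation, equal loss in both arms, and no information from those who drop out. This is a minor error in size but a plain one, in a figure by which retention will be judged.

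**What to change.** Restate the sentence in Sample size and power, for example:

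> Recruiting 31 participants per arm retains the required 26 per arm with drop-out of up to 16% at 12 months; at 20% drop-out about 25 per arm remain, with power of about 78% (normal approximation; about 77% by t test).

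This costs one sentence and leaves the target of 62, in that section and in the Abstract, unchanged. The claim becomes slightly less favourable.

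If the sponsor prefers to keep the 20% allowance, the target becomes 33 per arm. The total in the Abstract then changes from 62 to 66, which means four more participants. Either choice removes the inconsistency.
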